**Figure 1 F1:**
[figure not shown]
**The application of pulsed electromagnetic fields on the ankle, generated in the green coil and attached with the elastic band (I-ONE, IGEAmedical, Carpi, Italy)**.

### Standard treatment and investigational treatment

All surgical procedures will be performed using a standardized technique [2]. Briefly, the ankle joint is approached by arthroscopy using an anterior or posterior approach. The OD is identified with a probe and debrided with a curette and bonecutter shaver. All unstable bone and cartilage are removed. After full debridement, the subchondral bone is perforated with a microfracture awl, with intervals of approximately 3 mm. At the end of the procedure a pressure bandage is applied.

After surgery the protocol-based rehabilitation program, guided by a physiotherapist, will be equal in both groups. It will be initiated with partial (eggshell) weight bearing on crutches, as tolerated, and progressed to full weight bearing over a period of six weeks. During this period active non-weight-bearing and partial weight-bearing sagittal range of motion exercises are encouraged, i.e., 15 minutes twice daily. After this six week' period, resumption of sports will be permitted as tolerated, and will not be directed by the clinician.

In both groups the investigational treatment (active PEMF-treatment or sham device treatment) will start within three days after surgery. It will be applied four hours daily (in one or two sessions) for a period of 60 days [37,38]. The patients' compliance will be monitored by a clock inside the device that records the hours of stimulation.

The prescription of nonsteroidal anti-inflammatory drugs will be avoided due to their negative effect on bone regeneration [39]. The use of paracetamol will be allowed up to a maximum dose of 4 g/d and will be discontinued one week before the visits at baseline, 1 month, 2 months, 6 months and 1 year.

### Outcome measures

The combined primary outcome measures are:

(a) the number of patients that resume and maintain sports during 12 months follow-up, and

(b) the time to resumption of sports, defined by the AAS.

Secondary outcome measures are:

- time to resumption of work,

- American Orthopaedic Foot and Ankle Society – Ankle-Hindfoot Scale (AOFAS-AHS),

- Foot and Ankle Outcome Score (FAOS),

- quality of life (EuroQol-5D),

- pain (Numeric Rating Scale),

- satisfaction (Numeric Rating Scale),

- computed tomography, and

- adverse events.

### Definitions

#### Primary outcome measures

Because there is no consensus as to defining what actual resumption of sport is – as Saxena and Eakin stated [4] – we define time to resumption of sports as the time after arthroscopy (weeks) until initiation of any sport with a minimum level of the pre-symptoms level minus 1 point on AAS, and maintained for at least 30 days. If a patient's activity level decreases to below the minimum level within 30 days after sport resumption, the resumption date will not be counted. To evaluate the level of sport activity, we will use the AAS that has been developed and validated by Halasi and associates [35]. This 10-point score is based on the type and level of sport or work, with 0 points indicating the lowest activity and 10 points indicating the highest activity (Table 1).

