### Inclusion criteria

• Patients with a symptomatic OD of the talus who are scheduled for arthroscopic debridement and microfracture [2]

• OD diameter < 15 mm on CT (in three dimensions: medial-lateral, anterior-posterior and superior-inferior)

• Ankle Activity Score (AAS) ≥ 4 before symptoms (Table 1) [35]

**Table 1 T1:** Ankle Activity Score by Halasi et al. [35]

		Ankle Activity Score^a^		
Category	Sports and Activities	T	C	R

10	American football	10	9	8
	Basketball	10	9	8
	Gymnastics	10	9	8
	Handball	10	9	8
	Rugby	10	9	8
	Soccer	10	9	8
9	Hockey	9	8	7
	Korfball	9	8	7
	Martial arts: judo, karate, kung fu, taekwondo	9	8	7
	Orienteering	9	8	7
	Rhythmic gymnastics	9	8	7
	Volleyball	9	8	7
8	Boxing	8	7	6
	Freestyle snowboarding	8	7	6
	Ice hockey	8	7	6
	Tennis	8	7	6
	Wrestling	8	7	6
7	Aerobics, fitness	7	6	5
	Badminton	7	6	5
	Baseball	7	6	5
	Cross-country running (running on uneven ground)	7	6	5
	Modern pentathlon	7	6	5
	Squash	7	6	5
	Surfing, windsurfing	7	6	5
	Table tennis	7	6	5
	Track and field: field events	7	6	5
	Water skiing	7	6	5
6	Dancing	6	5	4
	Fencing	6	5	4
	Floorball	6	5	4
	Mountain and hill climbing	6	5	4
	Nordic skiing	6	5	4
	Parachuting	6	5	4
	Softball	6	5	4
	Special professions and working activities^b^	6		
5	Diving	5	5	4
	Scuba diving	5	5	4
	Skating, in-line skating	5	5	4
	Track and field: track events (running on even ground)	5	5	4
	Triathlon	5	5	4
	Weightlifting, body building	5	5	4
	All competitive sports of categories 4 and 3 with seasonal conditioning	5		
	Heavy physical work	5		
4	Alpine skiing and snowboarding	4	4	4
	Bowling/curling	4	4	4
	Golf	4	4	4
	Mountain biking/bmx	4	4	4
	Power lifting	4	4	4
	Sailing	4	4	4
	Physical work	4		
3	Cycling	3	3	3
	Equestrian	3	3	3
	Motorsports, technical sports	3	3	3
	Rowing, kayaking	3	3	3
	Shooting, archery	3	3	3
	Water polo and swimming	3	3	3
	Able to walk on any uneven ground	3		
2	No sports, everyday activities not limited	2		
1	Able to walk on even ground, but everyday activities limited	1		
0	Unable to walk, disabled because of ankle problems	0		

^a^T, top level (international elite, professional, national team, or first division); C, lower competitive levels; R, recreational level (participation should be considered only if it exceeds 50 hours per year).

^b^Special professions include ballet dancer, professional soldier, special rescue worker, stuntperson, and so forth.

If multiple options are applicable, the highest level is chosen.

• Age 18 years or older

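### Work can set the pre-symptom AAS but only sport counts as resumption, so some full recoveries are scored as failures

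*Protocol article*

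**What the plan says.** The protocol article settles this in three places.

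- **Inclusion criteria.** Eligibility requires "Ankle Activity Score (AAS) ≥ 4 before symptoms". Nothing says that the score must come from sport, or that the patient must have played any.
- **Table 1 and its footnotes.** Work has its own rows: special professions score 6, heavy physical work 5 and physical work 4. Where several rows fit, "If multiple options are applicable, the highest level is chosen". Recreational sport counts only above 50 hours a year.
- **Definitions, Primary outcome measures.** On the scale: "This 10-point score is based on the type and level of sport or work". Resumption is "initiation of any sport with a minimum level of the pre-symptoms level minus 1 point on AAS", maintained for at least 30 days.

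Resumption of work is a separate secondary outcome. Under Recording sport resumption, the diary captures the type and level of each sport and, separately, the return to work.

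**The concern.** The reference level is the maximum over work and sport, but the event that must reach it is a sport. When the job scores two or more points above the patient's own sport, the one-point allowance does not close the gap. A heavy manual worker who cycled before symptoms and is back at both job and cycling has recovered fully, yet is a non-resumer under the rule.

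Such patients lower the proportion resuming in both arms, whatever the device does. They also contribute no time to the *t*-test, which under Statistical methods is confined to patients who resume. Both components of Fisher's combination test therefore lose information. This is more than a missing detail: the rule as written gives a wrong classification on the primary endpoint, and it also governs who is enrolled.

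**Working it through.** **1. Which patients are affected.** Inputs are the scores in Table 1. Pre-symptom AAS = max(work score, sport score). The patient's own sport counts if its score ≥ pre-symptom AAS − 1.

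| Work row | Score | Sport score needed | Own sport that does not count |
|---|---|---|---|
| Physical work | 4 | 4 − 1 = 3 | none: every listed sport scores at least 3 |
| Heavy physical work | 5 | 5 − 1 = 4 | category 3 sports (3 at every level) |
| Special professions | 6 | 6 − 1 = 5 | category 3 (3), category 4 (4), recreational category 5 and 6 (4) |

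One row narrows this further. "All competitive sports of categories 4 and 3 with seasonal conditioning" scores 5, so a patient who competes on those terms in a category 3 or 4 sport passes in every case. Patients who qualify on a work row and had no countable sport have nothing to return to. They could meet the definition only by starting a sport.

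**2. The plan's own power.** Inputs from Sample size: 30 per arm, 0.50 versus 0.75, means 15 versus 12 weeks, SD 4, Fisher's combination test at 0.05. The statistic is −2(ln p₁ + ln p₂), referred to chi-square with 4 df (critical value 9.49). Here p₁ is from the uncorrected chi-square test and p₂ from the pooled *t*-test among resumers. Simulation gives about 78% at 30 per arm and about 80% at 31, so the stated 80% is reproduced to within 2 points.

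**3. Sensitivity to the affected share f.** The documents do not give f, so it is assumed.

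Scenario A: 0.50 and 0.75 hold only for unaffected patients, and affected patients never resume. The proportions become 0.50(1 − f) and 0.75(1 − f), and the difference becomes 25(1 − f) points.

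Scenario B: 0.50 is the overall control rate and only the gain is diluted. The treatment proportion is 0.50 + 0.25(1 − f).

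| f | A: proportions | A: difference (points) | A: power | B: power |
|---|---|---|---|---|
| 0 | 0.500 / 0.750 | 25.0 | 78% | 78% |
| 5% | 0.475 / 0.7125 | 23.75 | 74% | 75–76% |
| 10% | 0.450 / 0.675 | 22.5 | 70% | 73% |
| 20% | 0.400 / 0.600 | 20.0 | 61% | 68% |

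Scenario C: 0.50 and 0.75 both describe all enrolled patients. Then nothing is lost against the plan, because the dilution is already in its figures.

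**The case against.** **A sport-only reading is available.** The definition introduces the AAS as a way to evaluate sport activity, the diary records sport type and level, and a condensed article may leave scoring instructions to the full protocol. This does not remove the problem. The next sentence names work as a basis of the score, and Table 1 keeps both the work rows and the highest-level rule. At best two readings remain, and assessors in five centers could classify the same patient differently.

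**Stronger readings do not hold.** A reader might infer the following:

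- *All manual workers with low-category sports are barred.* They are not. With physical work (4) the needed score is 3, so return to cycling or swimming counts.
- *The affected patients cannot succeed.* The definition accepts any sport at the required level. The heavy worker who cycled could qualify with golf or mountain biking, which score 4 recreationally. What cannot count is return to the patient's own sport.
- *They are failures on both primary outcomes.* Non-resumers are left out of the comparison of mean times; they are not scored as failures there.
- *Return to work is mixed into the endpoint.* It never counts as an event. Work can only raise the reference level.

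**The size is uncertain.** This stands. No share is given, the Background describes patients as usually young and athletic, and the 50% is stated for patients generally, without excluding this group. Scenario C shows that the loss against the plan may be nil.

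**Conclusion.** The mismatch is real but narrow. It affects patients with heavy physical work whose only sport scores 3, patients with a special profession whose sport scores 4 or less, and patients eligible on work alone. The first two groups are scored as not resuming after full return to their own work and sport, unless they move to a higher-scoring sport.

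The expected consequence is misclassification and dilution in both arms. A reader might infer bias in the treatment comparison, but randomization should spread these patients over both arms and the documents give no reason to expect otherwise.

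The size cannot be stated. The fall in power from about 78% to 74% at 5% affected, or 70% at 10%, requires that the planned rates exclude these patients and that none of them resumes. For a given share it is an upper bound. The case for correction rests on the misclassification, not on that power loss.

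**What to change.** **Definition.** Under Primary outcome measures, state that the reference for the one-point allowance is the pre-symptom AAS from the sport rows of Table 1 only. Score postoperative resumption on the same rows, and leave work to the work-resumption outcome.

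**Inclusion criterion.** Reconcile the threshold of 4 with this for future patients, by requiring either a countable pre-symptom sport or a sport-only AAS of at least 4.

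**Patients already enrolled.** Keep them in the intention-to-treat analysis. Derive the sport-only reference from the baseline type of sport, blinded to allocation. Those with no pre-symptom sport keep the protocol's present definition, with a sensitivity analysis that excludes them.

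**Cost.** A short change to two sections. Type of sport and profession are already recorded at baseline, and category 3 and 4 sports score the same at every level apart from the seasonal-conditioning row. For category 5 and 6 sports the level of play matters and must be known. Work-only candidates become ineligible. Under the sport-only threshold of 4, so do heavy workers whose only sport scores 3; requiring just a countable sport would keep them.

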#### Secondary outcome measures

Resumption of work is defined as the ability to perform normal work exercises without any deficits in work quality [40]. The AOFAS-AHS is a frequently used combined objective-subjective 100-point scale which devotes 40 points to pain, 50 points to function, and 10 points to alignment [41]. The subjective part was recently validated [42]. The FAOS is a subjective 42-item questionnaire assessing five subscales: pain, other symptoms, activities of daily living, sports, and quality of life. All items are scored on a Likert-scale, and each of the five subscales is transformed to a score of 0 (worst) to 100 (best). The original English version has been validated [43], and the Dutch translation is currently being validated in our institution. The EuroQol (EQ-5D) is a validated and extensively used general health questionnaire to measure quality of life [44,45]. It comprises five dimensions: mobility, self-care, usual activities, pain/discomfort and anxiety/depression. Each dimension is marked as either no problems, some problems, or severe problems, which results in a 1-digit number expressing the level selected for that dimension. The digits for five dimensions are combined in a 5-digit number describing the respondent's health state. The numeric rating scale (NRS) for pain consists of an 11-point scale (0 – 10) which represents the whole spectrum of no pain up to the worst pain imaginable [46]. Pain at rest and pain when running will be measured. Patients' satisfaction will be measured using a NRS where 0 indicates no satisfaction and 10 indicates maximally possible satisfaction.

To objectively assess bone repair we will obtain multislice helical CT-scans of the affected ankles at baseline and one year after surgery (Figure 2). CT-scanning has been proven to be accurate in the detection and follow-up of ODs of the talus, regarding location and extent as well as healing of the defect [47,48]. The scanning protocol will involve "ultra high resolution" axial slices with an increment of 0.3 mm and a thickness of 0.6 mm, and multi-planar coronal and sagittal reconstructions of 1 mm [49]. The scans will be analyzed twice by a single physician, blinded to both treatment allocation and clinical outcome, measuring completeness, thickness, and level of the subchondral plate (i.e., flush, depressed, or proud) [50]. Additionally, bone volume filling of the defect after one year will be measured, and graded as good (67% to 100%), moderate (34% to 66%), or poor (0% to 33%) [51].

### Adverse events

Any (serious) adverse event during the trial period will be recorded. Adverse events are defined as any undesirable experience occurring to a subject during a clinical trial, whether or not considered related to the investigational treatment, e.g. infection, numbness, or paraesthesia. A serious adverse event (SAE) is any undesirable experience associated with the use of the investigational treatment that results in death, is life threatening (at the time of the event), requires hospitalization or prolongation of existing inpatients' hospitalization, or results in persistent or clinically relevant disability or incapacity. All SAEs will be reported to the central Medical Ethics Committee according to their requirements. Patients suffering from a SAE will stop their PEMF- or sham-treatment.

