### Data acquisition and follow-up

Participating patients will be assessed at the following time points (Table 2):

**Table 2 T2:** Patient assessment.

	Physician									Patient			
	
	Baseline characteristics*	Sport resumption	Work resumption	AAS	AOFAS-AHS	CT	Wound inspection	Compliance	Adverse events	FAOS	EQ-5D	NRS pain	NRS satisfaction
**Preoperative**	X			X	X	X				X	X	X	

**1–2 weeks**							X	X	X				

**1 month**			X					X	X		X	X	X

**2 months**		X	X	X	X		X	X	X	X	X	X	X

**6 months**		X	X	X							X	X	

**1 year**		X	X	X	X	X			X	X	X	X	X

* Baseline characteristics include age, gender, weight, height, affected side, duration of symptoms, type of sport and profession, past medical history, smoking status, and size, localization and classification of osteochondral defect on computed tomography.

AAS = Ankle Activity Score; AOFAS-AHS = American Orthopaedic Foot and Ankle Society – Ankle-Hindfoot Scale; CT = Computed Tomography; FAOS = Foot and Ankle Outcome Score; EQ-5D = EuroQol questionnaire; NRS = Numeric Rating Scale.

1. *Preoperatively*: information letter, informed consent, baseline characteristics (age, gender, weight, height, affected side, duration of symptoms, past medical history, smoking status), type of sport and profession, AAS (2×: before symptoms and at preoperative assessment), AOFAS-AHS, FAOS, EQ-5D, NRS pain (2×: at rest and when running), CT: size, localization and classification of the OD (Table 3) [52]

**Table 3 T3:** Computed tomography classification of osteochondral defects of the talus [52].

Grade	Description
I	Compression
II	Partially fractured but undisplaced
III	Completely fractured but undisplaced
IV	Displaced fracture
V	Radiolucent (fibrous) defect

2. *1–2 weeks postoperatively*: check compliance, (S)AEs, wound inspection (healing, signs of infection)

3. *1 month postoperatively*: check compliance, (S)AEs, resumption of work, EQ-5D, NRS pain (at rest) and satisfaction

4. *2 months postoperatively*: check compliance, (S)AEs, resumption of sport and work, AAS, AOFAS-AHS, FAOS, EQ-5D, NRS pain (at rest and when running, if applicable) and satisfaction, wound inspection, stop PEMF- or sham-treatment

5. *6 months postoperatively*: resumption and maintenance of sport and work, AAS, EQ-5D, NRS pain (at rest and when running)

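### Seriousness is tied to association with the device, so serious events attributed to surgery may not be reported as SAEs; and no adverse-event check is scheduled between 2 months and 1 year

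*Protocol article*

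**What the plan says.** The section Adverse events of the protocol article opens with a general duty: "Any (serious) adverse event during the trial period will be recorded". It defines an AE as "any undesirable experience occurring to a subject during a clinical trial, whether or not considered related to the investigational treatment". The next definition is narrower: "A serious adverse event (SAE) is any undesirable experience associated with the use of the investigational treatment", followed by the usual seriousness criteria (death, threat to life, hospital admission, lasting disability).

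Two actions in the same section depend on the SAE label. One is reporting: "All SAEs will be reported to the central Medical Ethics Committee according to their requirements". The other is treatment: "Patients suffering from a SAE will stop their PEMF- or sham-treatment".

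The section Data acquisition and follow-up schedules the checks. Item 4, the 2-month visit, includes one: "check compliance, (S)AEs, resumption of sport and work, AAS, AOFAS-AHS, FAOS, EQ-5D". Item 5, the 6-month visit, lists only "resumption and maintenance of sport and work, AAS, EQ-5D, NRS pain (at rest and when running" and ends there. The 6-month row of Table 2 likewise has no mark under adverse events. The 1–2 week, 1-month and 1-year visits all have one.

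Adverse events are a secondary outcome under Outcome measures, and Statistical methods plans a comparison of their number between the arms.

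**The concern.** Seriousness and relatedness are separate questions. The SAE definition merges them, although the AE definition just before it keeps them apart with the words "whether or not considered related to the investigational treatment". If an admission after surgery is put down to the arthroscopy, it meets a seriousness criterion but not the association condition, and the reporting sentence then does not clearly reach it.

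Individual attribution is hard in this trial. Every patient has had the arthroscopy and starts the device within three days of it. The section's own examples of adverse events (infection, numbness, paraesthesia) could each plausibly be ascribed to the operation. Patients, treating physicians and assessors are blinded. The sham arm allows relatedness to be judged by comparing groups, so it is better to classify serious events first and judge cause afterwards.

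The schedule is a separate weakness. The promise to record every event in the trial period has no scheduled prompt behind it for most of follow-up. At stake are the completeness of a secondary outcome and the timeliness of SAE reports, not the primary result.

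**Working it through.** The plan gives no figure to reproduce here. The check compares definitions and reads the schedule.

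**1. The two definitions side by side**

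| Element | AE | SAE |
|---|---|---|
| Relatedness | Irrelevant: "whether or not considered related to the investigational treatment" | Required on the natural reading: association with use of the investigational treatment |
| Recorded during the trial | Yes | Yes |
| Reported to the central ethics committee | Not stated | Yes |
| Linked to stopping the device | Not stated | Yes |

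Take a hospital admission for a wound infection attributed to the arthroscopy. It is an AE and must be recorded. It meets a seriousness criterion. It is an SAE only if it is also judged associated with the device. If it is not so judged, neither the reporting sentence nor the stopping sentence applies to it as written.

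**2. Scheduled AE checks (Table 2 and items 2 to 6)**

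| Visit | AE check |
|---|---|
| 1–2 weeks | Yes |
| 1 month | Yes |
| 2 months | Yes |
| 6 months | No (table and list agree) |
| 1 year | Yes |

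- Longest interval between scheduled checks: 12 − 2 = 10 months.
- Share of the 12-month follow-up: 10 / 12 = 83%.
- With a check at 6 months: 6 − 2 = 4 months and 12 − 6 = 6 months.

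**3. Where the interval lies relative to treatment.** Treatment starts within three days of surgery and lasts 60 days, so it ends by about day 3 + 60 = 63. Item 4 places its end at the 2-month visit. The 10-month interval is therefore essentially all off treatment.

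**4. Where it lies relative to return to sport.** Sample size assumes mean return at 15 weeks in the control group and 12 weeks with active treatment, that is 15 × 7 = 105 and 12 × 7 = 84 days. Both fall after the 2-month visit (about day 61). Events linked to resuming sport would thus tend to fall in the interval without a scheduled check.

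**5. Other routes of capture.** The diary described under Recording sport resumption covers sport and work only. Quality assurance includes AE registration among the monitoring checks, but each center is monitored twice: once at an early point tied to the fourth included patient's two-month follow-up, and once after the last patient's last visit. Neither replaces a question put to each patient at 6 months.

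**The case against.** Several points on the other side stand, and they limit the finding.

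- **Recording.** A reader might infer that serious surgical events, or events between months 2 and 12, go unrecorded. The document does not support this. All AEs in the trial period must be recorded whatever their cause, the 1-year visit asks about them, and nothing confines recording to visits with a mark in Table 2. What may be lost is the SAE label, the committee report and timeliness.
- **Between-arm comparison.** A reader might infer that the SAE wording removes the safety comparison between arms. It does not: the planned test uses the number of AEs, which are all-cause. Only a tabulation restricted to serious events would rest on the narrower label.
- **Bias.** Both blinded arms share one schedule. Under-ascertainment in both is more plausible than a distorted difference, and no bias is shown.
- **Exposure.** Three of the four scheduled checks cover the treatment period. Concentrating them there is a defensible choice, and Table 2 and the visit list agree, so the missing check is not an inconsistency between the two.
- **Wording.** Association with use could be read as temporal rather than causal. The contrast with the AE definition favours the causal reading but does not settle it. The committee's own requirements are not shown and may be broader.
- **Side effect of a simple deletion.** Striking the association phrase would also widen the event set that triggers the stopping sentence, which is a clinical matter.

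What these points leave untouched is that the two definitions differ in scope, that committee reporting depends on the narrower one, and that a visit which takes place anyway omits the AE question.

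**Conclusion.** The point holds in a limited form. On the more natural reading of the SAE definition, a serious event attributed to the arthroscopy is recorded as an AE but may not be classed as an SAE or reported to the ethics committee. On the other reading, the wording is ambiguous enough for five centers to apply it differently. Separately, one scheduled check at 1 year has to cover 10 of the 12 months of follow-up, all essentially after treatment. That risks under-recording and late reporting, in both arms, of a declared secondary outcome.

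How many events would be affected cannot be derived, because the document gives no expected AE or SAE rate. No sample size, power or primary-outcome figure changes. This is an inexpensive improvement to safety ascertainment and not a threat to the trial's main conclusion. It rests on the causal reading of the association phrase and on the reporting procedure being as the article describes it.

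**What to change.** 1. In Adverse events, for recording and committee reporting, define an SAE by the seriousness criteria alone, independently of relatedness. Record the relatedness judgement as a separate field in the Case Report Form.
2. Add an AE check to the 6-month visit, both in Table 2 and in item 5 of the visit list.
3. Reconcile the AE, SAE and stopping sentences, because the stopping sentence uses the same term and its reach would otherwise change with the definition. Which events should lead to stopping is for those clinically responsible; no rule is proposed here.

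The cost is a change of wording, one additional form field, a few more SAE reports, and one more question at a visit that already takes place.
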